## Abstract

**Background:**

Parkinson’s disease with mild cognitive impairment (PD-MCI) is one of the primary non-motor symptoms of Parkinson’s disease (PD). PD-MCI represents an early stage of cognitive impairment in PD and serves as a potential precursor to PDD. To date, research on the treatment of mild cognitive impairment in PD remains limited. Acupuncture, a classical therapeutic modality in Traditional Chinese Medicine, exhibits superior therapeutic outcomes to pharmacotherapy for mild cognitive impairment while avoiding drug-associated adverse effects.

**Objective:**

This randomized, single-blind clinical trial aims to evaluate the efficacy and safety of acupuncture for PD-MCI. To improve the credibility of acupuncture research evidence through employing a sham acupuncture device as a control.

**Methods and analysis:**

This is a prospective, sham-controlled, subject-blinded and assessor-blinded trial, which conducted at a single center in China. A total of 72 eligible PD-MCI volunteers will be randomized using a simple randomization method in a 1:1 ratio into the acupuncture group and the placebo acupuncture group to receive either acupuncture or placebo acupuncture for 20 sessions over a succession of 5 weeks. The primary outcome measure will be the Montreal Cognitive Assessment Scale (MoCA) score. The secondary outcome measures will be the scores of Mini-Mental State Examination (MMSE), Unified Parkinson’s Disease Rating Scale Motor Examination (UPDRSIII) and the level of neurofilament light polypeptide (NfL) and glial cell-derived neurotrophic factor (GDNF). The evaluation will be assessed before and after treatment.

**Discussion:**

This study represents the first randomized, single-blind clinical trial investigating acupuncture treatment for cognitive dysfunction in Parkinson’s disease. An auxiliary device designed by our team, featuring a flat-head needle and adjustable sleeve, will be used for placebo acupuncture procedure to achieve a single-blind effect. Serum NfL and GDNF levels will be incorporated to elucidate the mechanisms underlying acupuncture’s effects and explore specific biomarkers of PD. The aim of this study is to provide reliable clinical evidence for the treatment of PD-MCI and improve patients’ survival and quality of life.

**Clinical trial registration:**

https://www.chictr.org.cn/, identifier ChiCTR2400082082.

## Introduction

1

Parkinson’s disease (PD) represents a progressive neurodegenerative disorder primarily affecting individuals aged 50 years and older. While its clinical manifestations are mainly characterized by bradykinesia, resting tremor, and rigidity, the disease’s substantial burden also often stems from its non-motor symptoms such as mental disorders, cognitive impairment, sleep disorders, and sensory disorders. Among these, Parkinson’s disease with mild cognitive impairment (PD-MCI) has emerged as a particularly significant concern, affecting 30–40% of PD patients and progressing to Parkinson’s disease dementia (PDD) at an annual rate of 6–15% (1). PD-MCI as both a clinical precursor and modifiable risk factor for PDD (2), highlighting the critical importance of early detection and intervention.

At present, the pathogenesis of PD-MCI remains incompletely understood. Relevant studies suggest the involvement of neurotransmitter system impairments, such as dopaminergic and cholinergic systems (3, 4). In clinical practice, while cholinesterase inhibitors and dopamine receptor agonists constitute the mainstay of PD-MCI pharmacotherapy, their clinical benefits remain suboptimal and are frequently accompanied by adverse effects. Therefore, more treatment options for PD-MCI need to be explored.

Acupuncture, as a well-established therapeutic approach in Traditional Chinese Medicine (TCM), demonstrates clinical advantages including procedural simplicity and favorable safety characteristics. It has gained widespread clinical adoption as a non-pharmacological therapy. In recent years, many researches show that acupuncture can modulate the brain activities through Functional magnetic resonance imaging (fMRI) and EEG (5–7). It was proved that acupuncture promotes cognitive function and affords neuroprotective effects against inflammation in animal experiment (8). Accumulated clinical evidence indicates that acupuncture can improve cognitive function by regulating neurotransmitters, enhancing neurotrophic factor signaling, and reducing cell apoptosis (9). More importantly, it was demonstrated that acupuncture treatment could ameliorate the non-motor symptoms, quality of life and activities of daily living in PD patients (10).

This randomized controlled trial is designed based on previous acupuncture research. It aims to evaluate the cognitive function improvement in PD-MCI patients receiving either verum or placebo acupuncture. In this study, we focus on the clinical efficacy of acupuncture for PD-MCI in order to provide an evidence-based assessment of acupuncture’s therapeutic value. We hope that we can expand the clinical treatment option for PD-MCI through the study, help to delay the disease progression, and enhance the quality of life of PD patients.

## Materials and methods

2

This study will be a prospective, single-blind, randomized controlled clinical trial targeting Chinese PD-MCI patients. The trial will be conducted at the First Affiliated Hospital of Guangzhou University of Chinese Medicine.

The ethics committee of the First Affiliated Hospital of Guangzhou University of Chinese Medicine has approved the research protocol, which will follow the Declaration of Helsinki. The protocol has also been registered in the Chinese Clinical Trial Registry (ChiCTR2300074675).

A total of 72 eligible PD-MCI volunteers will be included in this study, and the flowchart is shown in Figure 1.

**Figure 1 fig1:**
[figure not shown]
Flowchart of the trial.

### Diagnostic criteria

2.1

Diagnostic criteria for PD refer to the Movement Disorder Society Clinical Diagnostic Criteria for PD (2015) (11). The diagnostic criteria for mild cognitive impairment in PD refer to the Diagnostic Criteria for Mild Cognitive Impairment in Parkinson’s Disease formulated by the International Association of Dyskinesia in 2012 (12).

#### Inclusion criteria

2.1.1

Meet the diagnostic criteria for idiopathic PD and PD-MCI.Meet the diagnostic criteria of TCM tremor syndrome and stupidness.Patients aged 50–70 years.MoCA scale score range of 18 to 25.MMSE scale score range of 21 to 26.Hoehn-Yahr staging scale staged 1–3.Do not participate in other drugs, acupuncture and other treatments or clinical trials within 1 month.Voluntarily join the study and sign the informed consent.

#### Exclusion criteria

2.1.2

The exclusion criteria are as follows:

Do not meet the diagnostic criteria and inclusion criteria.Users of pharmaceutical products improving cognitive function, such as Donepezil, galantamine, memantine hydrochloride, etc.Diagnosed with severe mental complications such as major depression and schizophrenia.Cognitive dysfunction caused by other diseases.Had participated in other drug or acupuncture studies within 30 days of treatment initiation.Diagnosed with other severe illnesses such as stroke, hematopoietic system diseases, malignant tumors, etc.Allergic or intolerant to acupuncture.

### Sample size

2.2

Aligned with the study’s objective, Montreal Cognitive Assessment Scale (MoCA) was chosen as the primary outcome. According to the results of previous experiments and literature review (13, 14), the mean and standard deviation of MoCA scale in PD-MCI patients received acupuncture combined with anti-PD drug treatment were 25.32 and 4.34, while there were 21.48 and 4.44, respectively, in PD-MCI patients who received sham acupuncture combined with anti-PD drug treatment. PASS V.15.0 (NCSS, Kaysville, UT, United States) was used to calculate the sample size. We set 90% for power level and 5% for two-sided significance level. It was estimated that there were about 29 patients in each group, and considering the dropout rate of 20%, the total sample size needed for study is 72, with 36 patients in each group.

### Randomization

2.3

Subjects with PD-MCI who met the inclusion and exclusion criteria will be randomized using a simple randomization method in a 1:1 ratio into the acupuncture group and the placebo acupuncture group. Random sequence will be generated by a third party who do not participate in the study using SPSS Statistics 26.0 (IBM SPSS Statistics Inc., Chicago, United States).

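### Simple 1:1 randomization gives the planned 36 per group only about 9% of the time and leaves baseline MoCA unbalanced, and the unadjusted tests do not correct for it

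*Protocol article*

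**What the plan says.** Section 2.3 (Randomization) states that patients will be "randomized using a simple randomization method in a 1:1 ratio into the acupuncture group and the placebo acupuncture group"; the abstract says the same. On the list itself it adds only this: "Random sequence will be generated by a third party who do not participate in the study using SPSS Statistics 26.0". It names no block, stratum, minimization factor or fixed list length.

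Section 2.2 (Sample size) concludes that "the total sample size needed for study is 72, with 36 patients in each group". This comes from a calculation in which "It was estimated that there were about 29 patients in each group", raised for 20% dropout.

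Section 2.10 (Statistical analysis) compares the groups with an independent-samples t test or, if the data are not normal, a Mann-Whitney U test. It also mentions generalized estimating equations for non-normal repeated measurements. No baseline covariate is named anywhere in the section. Table 2 schedules MoCA at weeks 0, 5 and 25, so a baseline value will exist for every randomized patient who attends week 0.

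**The concern.** Under simple randomization each assignment is an independent draw, so 1:1 is the expected ratio and arm sizes vary by chance. A fixed 36 per group and that method do not describe the same list.

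The same holds for prognosis. Entry MoCA may lie anywhere from 18 to 25 (section 2.1.1), and baseline MoCA can be expected to predict MoCA five weeks later. Nothing in the allocation keeps it level between two arms of about 36, and the named between-group tests take no account of it. Part of any chance difference at week 0 would pass straight into the week-5 comparison. At stake are the precision of the primary result, how readily a reader can interpret it if the arms start apart, and an accurate account of how patients were allocated.

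**Working it through.** **1. The plan's own sample size.** Inputs from section 2.2: means 25.32 and 21.48, SDs 4.34 and 4.44, power 90%, two-sided 5%.

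- Difference: 25.32 − 21.48 = 3.84. Pooled SD: √((4.34² + 4.44²)/2) = 4.39. Standardized difference: 0.875.
- The noncentral t gives power 89.5% at 28 per arm and 90.5% at 29, so 29 per arm is reproduced.
- Dropout: 29/0.8 = 36.25 per arm. Strictly this rounds up to 37 (74 in total); the stated 72 is within two patients.

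**2. Arm sizes under simple randomization.** The size of one arm is Binomial(72, 0.5).

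| Split | Probability |
|---|---|
| exactly 36/36 | 9.4% |
| 32/40 or worse | 41.0% |
| 30/42 or worse | 19.5% |
| 28/44 or worse | 7.6% |

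An arm lies between 28 and 44 with probability 95.6%.

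**3. Effect on power.** Noncentral t with noncentrality 3.84/(4.39·√(1/n₁ + 1/n₂)), each arm multiplied by 0.8 for dropout.

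| Randomized | Completing | Power |
|---|---|---|
| 36/36 | 28.8/28.8 | 90.3% |
| 30/42 | 24.0/33.6 | 89.5% |
| 28/44 | 22.4/35.2 | 88.9% |
| averaged over all splits | | 89.9% |

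The average loss is 90.3 − 89.9 = 0.4 points. Taking 58 completers split at random instead gives 90.5% against 90.0%, a loss of 0.5 points.

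**4. Chance difference in baseline MoCA.** In SD units its standard error is √(1/n₁ + 1/n₂): 0.236 at 36/36 and 0.239 at 30/42. The chance of a difference beyond 0.25 SD is 29% and 30%. Equal arm sizes therefore do almost nothing for baseline balance.

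The article gives no baseline SD. I assume a range; 2.3 corresponds to scores spread evenly over 18–25. The 95% range at 36/36 is 1.96 × SD × 0.236:

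- SD 1.5: ±0.69 points
- SD 2.0: ±0.92 points
- SD 2.3: ±1.06 points

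For comparison, section 2.10 calls a change of 1.22 points clinically meaningful, and the planned difference is 3.84.

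**5. What adjustment would gain.** If week-5 MoCA rises by b points per baseline point, an unadjusted comparison of week-5 scores carries b times the chance baseline difference. ANCOVA removes that part and multiplies the standard error by about √(1 − r²), where r = b × (baseline SD)/(outcome SD). The outcome SD is taken as 4.39, and b is an assumption.

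- b = 1: r = 0.34, 0.46 and 0.52 for baseline SD 1.5, 2.0 and 2.3; the standard error falls by about 6%, 11% and 15%.
- b = 0.5: r = 0.17, 0.23 and 0.26; it falls by about 1% to 3%.

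**The case against.** The strongest reply is that there is no error. Thirty-six per group can be read as a target and 1:1 as an allocation probability, and the two can coexist. A pre-generated SPSS list might also have been built with exactly 36 of each code, in which case the split is certain. A condensed article need not describe how the list was built. This largely stands: the mismatch depends on taking simple randomization in its usual sense. But if the list has fixed arm sizes, the method is misnamed, and on either reading baseline MoCA stays unbalanced.

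It is also fair to say that simple randomization is valid, that its standard errors already allow for chance imbalance, and that it is the least predictable scheme. Predictability matters here because section 2.4 leaves the operating physicians unblinded, at a single centre. This stands too, and is why blocking is not pressed.

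On the analysis, section 2.10 does not say whether the between-group test uses week-5 scores or changes from baseline. Change scores would take baseline into account, but they are fully efficient only if the slope is 1; ANCOVA estimates the slope. A separate analysis plan may name a covariate. The article as written names unadjusted tests.

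A reader might infer more than the documents support:

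- That 36/36 practically never occurs. At 9.4% it occurs about once in eleven trials.
- That the trial is underpowered because a 30/42 split leaves about 24 completers in the smaller arm, under the 29 required. Power depends on both arms and stays at 89.5%. Even 36/36 leaves 28.8 per arm after 20% dropout.
- That drift during enrolment does harm. The article gives neither an enrolment period nor a time trend, and simple randomization is unbiased under drift.

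**Conclusion.** The point holds as one of precision and internal consistency. Taken literally, section 2.3 delivers the group sizes in section 2.2 about 9% of the time. The resulting loss of power is negligible, 0.4 to 0.5 points on average, and would not by itself justify changing the randomization. It does not make the treatment comparison biased or invalid.

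The part worth acting on is the analysis. A chance baseline difference of up to about 0.7 to 1.1 MoCA points is within ordinary variation, and the named tests leave it uncorrected. That range assumes a baseline SD of 1.5 to 2.3. The gain in precision from adjustment, about 1% to 15% in the standard error, also rests on an assumed slope of 0.5 to 1 and on the outcome SD in section 2.2 applying to this population.

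**What to change.** 1. In section 2.10, make the primary between-group comparison of week-5 MoCA an ANCOVA with treatment group and baseline MoCA as terms, in place of the unadjusted t test or Mann-Whitney test. Fix this before unblinding. It needs no new data and costs one degree of freedom.
2. Make sections 2.2 and 2.3 (and the abstract) agree. If allocation is truly simple, describe 36 per group as the expected size. If the list is restricted, name the scheme: a fixed-size list, or permuted blocks of varying, undisclosed size. This is a change of wording only, and it should describe what the third party actually produced.
3. Stratified blocking on baseline MoCA is optional. It would need a new list, could apply only to patients not yet randomized, and would make allocation somewhat more predictable to the unblinded acupuncturists. If it is adopted, keep the stratification factor or baseline MoCA in the primary model.

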### Blinding

2.4

To ensure the objectivity and accuracy of the results, this study adopts the single blind method to blind the subjects and the efficacy evaluator. Due to the limitations of needle operation, it is impossible to blind the operating physician, so the efficacy evaluator is a third party independent of the treatment operation and grouping to avoid subjective bias of the researcher. During the treatment, both groups of participants will be required to wear an eye mask to ensure the implementation of the blind method. At the end of the study, the blind will be uncovered and the participants will be informed of their group and acupuncture method.

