### Interventions

2.5

All the acupuncturists have obtained the doctor qualification certificate and have certain clinical experience. At the same time, before the start of the study, all treating physicians should undergo systematic training to ensure the consistency of operation. During the treatment process, each patient will be treated by the same acupuncturist throughout the entire procedure.

An auxiliary device designed by our team will be used during the acupuncture procedure in order to achieve a single-blind effect, which has passed the national utility model patent (patent number: ZL202121352221.7), and the article introducing the device has been published in the journal of Chinese Acupuncture & Moxibustion (15). This new auxiliary acupuncture device includes an acupuncture device and a placebo acupuncture device with exactly the same appearance, which consists of a base sticking to the skin and a sleeve. The base of the acupuncture device is hollow, while the placebo acupuncture device is sealed by a bonding layer (Figure 2). A flat head needle (Tianxie, Suzhou Medical Appliance Factory, Suzhou, China; 0.30 mm × 10 mm) (Figure 3) will be used for the procedure. The acupuncturist can adjust the sleeve according to the insertion angle of needles (Figure 4).

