#### Acupuncture group

2.5.1

Patients in the acupuncture group will receive 20 sessions of acupuncture (four times a week for 5 weeks), during which the original effective dose of anti-Parkinson’s disease drugs will be maintained. If there is a need to increase or decrease the dose under special circumstances, the change will be recorded in the case report form. Acupuncture points of the acupuncture group include Si Shen Zhen (Four acupoints, consisting of GV21, GV19, and next to GV20 1.5 cun bilateral), Shen Ting (GV24), Yin Tang (GV29), Su Liao (DU25), Shen Men (HT7) (bilateral), San Yin Jiao (SP6) (bilateral), Hegu (LI4) (bilateral), and Taichong (LR3) (bilateral). The positioning of Si Shen Zhen is in accordance with the “Application of Jin San Zhen acupoint Group” (16), and other acupoints are in accordance with the National Standard of the People’s Republic of China’s (GB/T 12346–2006) standard (17). Acupuncture will be processed with disposable, sterile steel needles (Tianxie, Suzhou Medical Appliance Factory, Suzhou, China; 0.25 × 25 mm, 0.25 × 40 mm). Patients will wear the blindfold throughout the treatment. After routine skin disinfection, the acupuncturist will affix the acupuncture device (Guangzhou Suixin Medical Equipment Co., LTD.) to the acupoint skin. 0.25 × 25 mm acupuncture needles will be used for Si Shen Zhen, Shen Ting (GV24) and Yin Tang (GV29) with a 15-degree angle. 0.25 × 40 mm acupuncture needles will be used for Su Liao (DU25), Shen Men (HT7) (bilateral), San Yin Jiao (SP6) (bilateral), Hegu (LI4) (bilateral), and Taichong (LR3) (bilateral) with a 90-degree angle. The acupuncture needle is inserted through the sleeve and the perforated base into the skin. The location of each acupoint is shown in Table 1 and Figure 5. The needle will be retained for 30 min.

**Table 1 tab1:** The location of each acupoint.

Acupoint	Location
Si Shen Zhen	Four acupoints, consisting of GV21, GV19, and next to GV20 1.5 cun bilateral
Shen Ting	On the head, 0.5 cun directly above the midpoint of the anterior hairline.
Yin Tang	On the head, in the depression between the medial ends of the two eyebrows.
Su Liao	On the face, at the tip of the nose, in the exact center.
Shen Men	In the anterior wrist region, at the ulnar end of the distal wrist crease, on the radial side of the tendon of the ulnar flexor muscle of the wrist.

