### Data management and quality control

2.9

To ensure trial consistency and accuracy, all team members will receive standardized training prior to study initiation. All members will receive training on the localization of acupoints, the application of sham needles, the evaluation of assessment scales, patient communication, as well as the methods and time points for follow-up. The researcher responsible for the assessment needs to be proficient in the questions and operations in the case report form (CRF), conduct an objective assessment of the subjects, and both the assessor and the subjects need to sign the CRF to ensure the reliability and integrity of the data. Researchers will strictly keep the case observation forms and set access permissions for electronic data, allowing only authorized personnel to enter, modify and view the data to ensure data security and protect the privacy of the subjects. Data quality will be monitored regularly to check whether the data are missing, wrong or invalid, and to ensure the completeness and rationality of the data.

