This study represents the first randomized, single-blind clinical trial investigating acupuncture treatment for cognitive dysfunction in PD. We employ a sham acupuncture device independently developed by our team as a control, thereby enhancing the credibility of evidence in acupuncture studies. Although some studies in acupuncture research have explored its therapeutic effects on cognitive impairment, no specific acupuncture intervention has yet targeted cognitive dysfunction in PD. Motor and non-motor symptoms in PD often interact and influence each other. Our study simultaneously assessed interventions for motor dysfunction, which may offer new insights into holistic management of PD. Additionally, the study explores the therapeutic mechanisms of acupuncture through clinical biofluid samples.

However, several limitations should be acknowledged. First, all enrolled cases are recruited from a single hospital, which may limit the generalizability of the findings across different regions. Second, minor stimulation may still occur in the sham group. Third, while patient blinding is successfully implemented, practitioners could not be blinded due to the nature of the acupuncture devices used in the study.

This study will provide reliable clinical evidence for the treatment of PD-MCI, thereby improving patients’ survival and quality of life while delaying or preventing its progression to PDD.

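### The assessor's blind rests on independence alone, the training rule works against it, and patient blinding is declared achieved with no check planned in this trial

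*Protocol article*

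**What the plan says.** **Who is blind.** Section 2.4 (Blinding) says that "this study adopts the single blind method to blind the subjects and the efficacy evaluator". The operator cannot be blinded, so the stated safeguard for the ratings is that "the efficacy evaluator is a third party independent of the treatment operation and grouping". During treatment, "both groups of participants will be required to wear an eye mask to ensure the implementation of the blind method".

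**What differs between arms.** In the real arm (2.5.1), "The acupuncture needle is inserted through the sleeve and the perforated base into the skin". The two devices look alike, but section 2.5 describes the real base as hollow, "while the placebo acupuncture device is sealed by a bonding layer". The sham needle is flat-headed. The points are the same in both arms. Table 1 places Su Liao "On the face, at the tip of the nose, in the exact center", Yin Tang between the eyebrows and Hegu on the back of the hand.

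**Who is trained.** Section 2.9 states: "All members will receive training on the localization of acupoints, the application of sham needles, the evaluation of assessment scales". It makes no exception for the researcher who does the ratings.

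**When ratings are done and what is checked.** Treatment runs four times a week for 5 weeks. Table 2 puts MoCA, MMSE and UPDRSIII at weeks 0, 5 and 25, and section 2.6.2.2 says only that the scales are rated before and after treatment. Table 2 has no row for an allocation guess or any other test of blinding.

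**What is claimed.** The limitations paragraph of the Discussion says "while patient blinding is successfully implemented". The support given, earlier in the Discussion, is validation of the device in the team's other trials.

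**The concern.** Independence keeps the assessor from being told the allocation. It does not keep the assessor from seeing it. The eye mask protects the patient's blind during a session and does nothing for the rater. What remains is that the rater should not know what to look for, and the training rule in section 2.9 removes even that if it is applied as written.

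The primary outcome is a rater-administered test and UPDRSIII is a motor examination, so a rater who suspects the arm can influence both. A patient's belief about allocation can also affect effort on a cognitive test. The Objective in the Abstract makes more credible evidence through the sham device a purpose of the trial. A plan that asserts successful patient blinding in advance and collects nothing to test it leaves that purpose unsupported by the trial's own data.

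**Working it through.** **1. The passages side by side.**

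| Element | Section | Effect on the blind |
|---|---|---|
| Assessor independent of treatment and grouping | 2.4 | Protects against being told the arm |
| Eye mask during treatment | 2.4 | Protects the patient only |
| Devices of identical appearance | 2.5 | Masks the procedure, not the skin once the device is removed |
| Real needle enters the skin; sham base sealed | 2.5, 2.5.1, 2.5.2 | Only one arm is meant to be punctured |
| All members trained in points and sham needles | 2.9 | Works against the assessor's blind |
| No blinding check scheduled | Table 2 | Failure would not be detected |
| Patient blinding reported as achieved | 3 | Claim made before any data exist |

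**2. Needles at exposed sites** (points from 2.5.1, locations from Table 1).

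- All needles: Si Shen Zhen 4 + GV24 1 + GV29 1 + DU25 1 + HT7 2 + SP6 2 + LI4 2 + LR3 2 = 15 per session.
- Plainly in view at a face-to-face rating: DU25 (nose tip) 1 + GV29 (brow) 1 + LI4 (hands) 2 = 4 of 15.
- Not counted: GV24, which Table 1 places 0.5 cun above the hairline, and HT7, which lies on the anterior wrist at the ulnar end of the crease. Counting these as well would give 4 + 1 + 2 = 7.
- Over 20 sessions: 4 × 20 = 80 of 15 × 20 = 300 insertions per patient.

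**3. The plan's own sample size**, reproduced because its SD and n are used in step 4.

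- Difference: 25.32 − 21.48 = 3.84.
- SD: √[(4.34² + 4.44²)/2] = √19.2746 = 4.39.
- Exact power of the two-sided 5% t test: 89.5% at n = 28 and 90.5% at n = 29, so 29 per group, as stated.
- Dropout: 29/(1 − 0.20) = 36.25, stated as 36 per group and 72 in total. The point about blinding does not depend on this figure.

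**4. Illustration of scale.** The bias b is my assumption; the documents give none. With no true effect, suppose the ratings shift the mean MoCA by b points in favour of acupuncture. The rejection rate is then the power of the t test with noncentrality b/[SD·√(2/n)] on 2n − 2 degrees of freedom. For b = 1, SD 4.39 and n = 29 the noncentrality is 1/(4.39 × √(2/29)) = 0.87.

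| Assumed shift b | SD 4.39, n = 29 | SD 4.39, n = 36 | SD 3.0 (assumed), n = 29 |
|---|---|---|---|
| 0 | 5.0% | 5.0% | 5.0% |
| 0.5 | 7.1% | 7.6% | 9.6% |
| 1.0 | 13.7% | 15.9% | 23.9% |
| 1.22 | 18.0% | 21.4% | 33.1% |
| 2.0 | 40.0% | 47.9% | 70.4% |

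The row at 1.22 is the responder threshold in section 2.10. The table shows what a given bias would do. It says nothing about whether such a bias will occur.

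**The case against.** Much of the surrounding detail is silence in a condensed article, and several stronger readings a reader might infer are not supported.

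- **Ratings on the day of session 20.** The article gives no interval, but it does not state a same-day rating. Four sessions a week leave three days without treatment, and the full protocol may set a window.
- **Assessor blinding declared successful.** It is not. The Discussion's statement covers patients only, in a paragraph that admits some sham stimulation and unblinded operators.
- **A claim with no basis.** The Discussion does cite validation of the device in other trials. Those sources are not at hand and cannot be judged either way.
- **Seven exposed sites.** On the article's own locations, four are plainly in view.
- **Marks reveal the arm and bias the result.** This is inference. Section 2.7 lists bleeding and hematoma as adverse events to record, not as routine marks. Both arms wear an adhesive base, which may itself leave traces.
- **All outcomes affected.** NfL and GDNF are ELISA measurements, and needle marks are not plausible at week 25.

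These points stand and they narrow the concern. They do not answer three things: the training rule is stated text and conflicts with the purpose of section 2.4; patient blinding is reported as achieved in a plan whose methods lie in the future; and a printed schedule of assessments has no place for a check. Validation in other trials does not show that the blind held here, with this assessor and these points.

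**Conclusion.** The point holds in a limited form. The assessor is declared blind on independence alone, and the training rule, read literally, gives that assessor the knowledge needed to recognise allocation in an arm where 4 of 15 needles per session puncture plainly visible skin. The trial schedules no check, so it cannot show that the blind held for the rater-administered week-5 MoCA, MMSE and UPDRSIII, while patient blinding is already reported as achieved.

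The documents do not establish that the blind will fail or that bias will enter the results. The rate of visible marks and the size of any bias are unknown, and the error rates above rest wholly on assumed shifts. The conclusion assumes that the training rule means what it says, and that the schedule in Table 2 is complete as regards blinding.

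**What to change.** 1. **Section 2.9:** exempt the outcome assessor from training in acupoint location and sham-needle application, keeping the training on the scales.
2. **Table 2:** add an allocation guess by each patient and by the assessor at week 5, before unblinding, and report a blinding index by arm.
3. **Table 2 or section 2.6:** state that the week-5 ratings are not done on the day of the last session, in both arms alike.
4. **Discussion:** say that patient blinding is intended and will be assessed, with the earlier device validation as supporting background.

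The cost is two case report form questions and a slightly later week-5 reading, with no extra patients or staff. A blinding index can partly reflect perceived benefit, since patients who feel better tend to guess real treatment, so it should be interpreted with caution.
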